## Abstract

**Background:**

Coronavirus disease 2019 (COVID-19), caused by the virus SARS-CoV-2, is spreading rapidly across the globe, with little proven effective therapy. Fever is seen in most cases of COVID-19, at least at the initial stages of illness. Although fever is typically treated (with antipyretics or directly with ice or other mechanical means), increasing data suggest that fever is a protective adaptive response that facilitates recovery from infectious illness.

**Objective:**

To describe a randomized controlled pilot study of core warming patients with COVID-19 undergoing mechanical ventilation.

**Methods:**

This prospective single-site randomized controlled pilot study will enroll 20 patients undergoing mechanical ventilation for respiratory failure due to COVID-19. Patients will be randomized 1:1 to standard-of-care or to receive core warming via an esophageal heat exchanger commonly utilized in critical care and surgical patients. The primary outcome is patient viral load measured by lower respiratory tract sample. Secondary outcomes include severity of acute respiratory distress syndrome (as measured by PaO2/FiO2 ratio) 24, 48, and 72 hours after initiation of treatment, hospital and intensive care unit length of stay, duration of mechanical ventilation, and 30-day mortality.

**Results:**

Resulting data will provide effect size estimates to guide a definitive multi-center randomized clinical trial. ClinicalTrials.gov registration number: NCT04426344.

**Conclusions:**

With growing data to support clinical benefits of elevated temperature in infectious illness, this study will provide data to guide further understanding of the role of active temperature management in COVID-19 treatment and provide effect size estimates to power larger studies.

## Introduction

Traditionally, fever has been treated because its metabolic costs were felt to outweigh its potential physiologic benefit in an already stressed host [1]. However, increasing data suggest that fever may be a protective adaptive response that should be allowed to run its course under most circumstances [2,3]. Higher early fever is associated with a lower risk of death among patients with an ICU admission diagnosis of infection [4,5]. Fever may enhance immune-cell function [6,7], inhibit pathogen growth [8–10], and increase the activity of antimicrobial drugs [11]. Fever potentially benefits infected patients via multiple mechanisms; *in vitro* and animal studies have shown that elevated temperatures augment immune function, increase production of protective heat shock proteins, directly inhibit microorganism growth, reduce viral replication, and enhance antibiotic effectiveness [3,12]. More rapid recoveries are observed from chickenpox [13], malaria [14], and rhinovirus [15] infections with avoidance of antipyretic medication, and many innate and adaptive immunological processes are accelerated by fever [16–18].

Randomized controlled trials have consistently failed to find benefits to treating fever of infectious etiology [16,19–25]. Reducing patient temperature to below normal in sepsis likewise has been found to be of no benefit, or harmful [26,27]. On the other hand, warming appears to have substantial benefits in sepsis. Multiple aspects of both humoral and cellular immunity (including antibody production, T lymphocyte trafficking, T cell adhesion and migration, heat shock protein 90 (Hsp90)-induced α4 integrin activation and signaling, and macrophage function) are boosted by elevated temperature [28]. A retrospective cohort study evaluating 1,264 patients requiring mechanical ventilation found that high fever (≥39.5°C) was associated with increased risk for mortality in mechanically ventilated patients; however, in patients with sepsis, moderate fever (38.3°C-39.4°C) was protective, and antipyretic medication was not associated with changes in outcome [29]. Prospective data show that afebrile patients have higher 28-day mortality (37.5% vs 18.2%), increased acquisition of secondary infections (35.4% vs. 15.9%), and suppressed HLA-DR expression suggestive of monocyte dysfunction over time [30]. As recently as the 1910’s, the “malaria fever cure” (inducing fever to treat a range of conditions, an approach known as “pyrotherapy”) was widespread, with the originator of the idea receiving the Nobel Prize in Medicine or Physiology in 1927 [31,32]. Currently, the UK National Institute for Health and Care Excellence (NICE) recommend not using antipyretic agents “with the sole aim of reducing body temperature in children with fever [16,33]”. Actively inducing hyperthermia by directly heating the body has been used in cancer treatment, with minimal adverse effects [34–37]. Hyperthermia has been found to have positive impacts on the immune system, causing increased levels of heat-shock proteins [28,38,39], which are directly related to antigen presentation and cross‐presentation, activation of macrophages and lymphocytes, and activation and maturation of dendritic cells [40]. A pilot study of external warming of septic patients (ClinicalTrials.gov Identifier: NCT02706275) has recently been completed.

Many viruses replicate more robustly at cooler temperatures, such as those found in the nasal cavity (33–35°C) than at warmer core body temperature (37°C) [41–45]. Coronavirus disease 2019 (COVID-19) currently has limited treatment options besides dexamethasone [46], but its causative virus (SARS-CoV-2) may behave similarly to other viruses susceptible to temperature changes [47]. Simulations of the receptor binding domain (RBD) of SARS-CoV-2 found high flexibility near the binding site, suggesting that the RBD will have a high entropy penalty upon binding angiotensin-converting enzyme II (ACE2), and that consequently, the virus may be more temperature-sensitive in terms of human infection than other coronaviruses [48]. Notably, fever has often abated by the time a COVID-19 patient requires mechanical ventilation [49]. Additionally, patients with severe COVID-19 tend to have a high viral load and a long virus-shedding period, suggesting that the viral load of SARS-CoV-2 might be a useful marker for assessing disease severity and prognosis [50]. The aim of this study is to determine the effect of active core warming patients diagnosed with COVID-19 and undergoing mechanical ventilation. We hypothesize that active core warming will reduce the severity of acute respiratory distress syndrome, reduce the duration of mechanical ventilation, and improve survival compared to standard of care.

### Study objectives

The purpose of the proposed pilot study is to determine if core warming improves respiratory physiology of mechanically ventilated patients with COVID-19, allowing earlier weaning from ventilation, and greater overall survival.

### Primary objective

Determine the change in viral load measured in lower respiratory tract sample after implementation of core warming of ventilated patients, and compare this change to patients undergoing standard care.

### Secondary objectives

Measure the impact of esophageal core warming on severity of acute respiratory distress syndrome as measured by PaO2/FiO2 ratio 24, 48, and 72 hours after initiation, and compare this to standard care.Compare the duration of mechanical ventilation of patients treated with core warming to patients treated with standard care.Compare the length of ICU and hospital stay of patients treated with core warming to patients treated with standard care.Compare the 30-day mortality of patients treated with core warming to patients treated with standard care.

## Methods

This is a single-center pilot study to evaluate if core warming improves respiratory physiology of mechanically ventilated patients with COVID-19, allowing earlier weaning from ventilation, and greater overall survival. The protocol was reviewed and approved by the Institutional Review Board of Washington University. The study is listed on ClinicalTrials.gov with identifier NCT04426344. This prospective, randomized study will include 20 patients diagnosed with COVID-19, and undergoing mechanical ventilation for the treatment of respiratory failure. Patients will be randomized in a 1:1 fashion with 10 patients (Group A) randomized to undergo core warming with an esophageal heat transfer device, and the other 10 patients (Group B) serving as the control group. Patients randomized to Group A will have the esophageal heat transfer device placed in the ICU or other clinical environment in which they are being treated after enrollment and provision of informed consent from appropriate surrogate or legally authorized representative. This study is posted on ClinicalTrials.gov with registration number: NCT04426344. The IRB of Washington University, St. Louis, is performing full review of the final protocol and expected to provide approval; the study will not start prior to IRB approval.

### Screening

Subjects will be recruited from the ICU or other clinical environment in which they are being treated (Emergency Department, step-down unit, etc.). Patients will be identified by the PI or other study investigators/coordinators as available, and will be restricted to those who have been undergoing mechanical ventilation for three days or less. All patients without a DNR order with a diagnosis of COVID-19 and meeting inclusion criteria will be eligible for screening for any exclusion criteria. Written informed consent for the research study will be obtained from patient’s surrogate or legally authorized representative prior to enrollment. A formal screening log will be maintained for the trial, and available data on patients not entered into the study will be compared to those entered into the study. Baseline variables of patients entered into the study will additionally be compared by randomization arm.

### Study intervention and monitoring

Participants who have a signed research study consent form (via surrogate or legally authorized representative) will be randomized in a 1:1 fashion to core warming or to standard of care (standard temperature management and treatment). The esophageal heat transfer device will be used according to FDA 510(k) labeling (for patient warming). Patient temperature measurements will be collected for both the device and standard-of-care arms during the study period (up to 72 hours). Device placement will be performed using standard protocol per instructions for use. The esophageal heat transfer device will be set to 42°C temperature after initial placement, and maintained at 42°C for the duration of treatment. All patients will have usual standard of care labs, vital signs, and imaging for patients in critical condition undergoing mechanical ventilation in the ICU. Specific parameters to be measured include PaO2 at regular intervals appropriate for patients undergoing mechanical ventilation, and FiO2 at the time of obtaining blood gases for PaO2 measurement, to allow calculation of P/F ratio.

Control group patients will be managed as per standard of care currently utilized in the ICU, which will include the use of other methods of temperature management as warranted. This would include warming with a forced air blanket only in hypothermic patients (core temperature < 36°C) or antipyretic therapy for febrile patients, as requested by the treating physician. Episodes of hypothermia are infrequent and transient in this population, and the current standard of care generally utilizes a permissive approach to fever (allowing patients to remain mildly febrile) which will continue in the control group without modification (no intentional elevation of temperature will be provided in the control group).

### Study endpoints

The purpose of this pilot study is to determine initial estimates on outcomes (viral load, PaO2/FiO2 ratio, duration of mechanical ventilation, and mortality) in order to determine adequate sample size to properly power definitive studies. Measurements will be compared at time points 24, 48, and 72 hours after initiation. Sampling for viral measurements will utilize lower respiratory tract samples, as these have been shown to be of greater sensitivity and reliability for patient monitoring [47,51,52].

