### Schedule of procedures and data collection

**Table pone.0243190.t001:** 

Study Phase	Screening	Randomization/Intervention Phase			Follow- up
Study Days	Day -1 to 0	Day 0	Day 1–2	Day 7, 14	Day 30
Informed Consent	X				
Review Inclusion/Exclusion Criteria	X				
Demographics	X				
Medical History/Interim History*	X		X		X
Physical Examination*	X		X		X
Vital Signs: Temperature, BP, HR, RR*	X		X		X
Height and Weight	X				
Pregnancy Test	X				
Clinical Laboratory Evaluation	X	X	X		
Respiratory tract viral load				X	
Ventilator settings	X	X	X		
APACHE III and SOFA scores	X	X	X		
Clinical Imaging	X	X	X		
Prior/Concomitant Medications	X				X
Randomization		X			
Temperature monitoring		X	X		
PaO2, FiO2, parameter recording		X	X		
Discharge			X		
Adverse Event / Unanticipated Problems Assessment		X	X		X

* Interim medical history, physical exam, and vitals will be collected via chart review from routine clinical care.

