### Statistical methods

We will utilize standard measures to report outcomes and measure differences between groups. Specifically, we will use descriptive statistics, including mean (standard deviation) and median (interquartile range). Kaplan-Meier plots of important time to event outcomes and measures will be produced. Normality will be assessed using histograms and the Kolmogorov–Smirnov test. Formal hypothesis testing is not planned for this pilot feasibility study.

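### The PaO2/FiO2 comparison makes no stated use of a baseline the trial can already derive, and the P/F recording row fits neither a pre-warming baseline nor the 72-hour value.

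*Protocol article*

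**What the plan says.** The secondary objective is to measure the effect of warming on "severity of acute respiratory distress syndrome as measured by PaO2/FiO2 ratio 24, 48, and 72 hours after initiation, and compare this to standard care". The list of secondary endpoints under *Primary study endpoints* repeats P/F at those three times, and *Study endpoints* adds that "Measurements will be compared at time points 24, 48, and 72 hours after initiation". The primary objective is worded differently, as a change: "Determine the change in viral load measured in lower respiratory tract sample after implementation of core warming of ventilated patients". No such wording is used for P/F.

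*Statistical methods* states that "we will use descriptive statistics, including mean (standard deviation) and median (interquartile range", mentions Kaplan-Meier plots and normality checks, and rules out formal hypothesis testing. The only stated use of baseline data is under *Screening*: "Baseline variables of patients entered into the study will additionally be compared by randomization arm".

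*Data collection* lists arterial blood gas among the clinical laboratory tests. In the schedule table, the rows for clinical laboratory evaluation and "Ventilator settings" are both marked at Screening, Day 0 and Day 1–2. The row "PaO2, FiO2, parameter recording" is marked only at Day 0 and Day 1–2. *Study intervention and monitoring* asks for "FiO2 at the time of obtaining blood gases for PaO2 measurement, to allow calculation of P/F ratio".

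**The concern.** A pre-treatment P/F can be derived from data already scheduled, yet no stated analysis of the outcome uses it. With 10 patients per arm, chance differences in baseline oxygenation are common, and part of any such difference persists into the follow-up values. *Study endpoints* says the pilot is meant to give estimates, P/F among them, for sizing definitive studies. The precision of those estimates is therefore what the trial delivers, and the absence of hypothesis tests does not remove the point. Group summaries alone also do not give the baseline–follow-up correlation, which a later trial would need if it planned an adjusted analysis.

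The schedule adds a practical problem. Day 0 is the day of randomisation and falls in the intervention phase, so a Day 0 P/F may come before or after warming starts. Counting from Day 0, 72 hours falls on Day 3, and the table has no column between Day 1–2 and Day 7.

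**Working it through.** The document states no power or precision figure for P/F, so there is none to reproduce.

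**Inputs.** From the document: 20 patients, 10 per arm, and P/F at 24, 48 and 72 h. Assumed, because the document gives neither: a common SD (results are in SD units) and the correlation r between baseline and follow-up, shown over a range.

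**1. Unadjusted comparison at one time.** SE = √(2/10) = 0.447 SD. The 95% half-width is 2.101 × 0.447 = 0.94 SD (t, 18 df).

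**2. Chance baseline imbalance.** The baseline difference between arms has the same SE. P(|difference| > 0.5 SD) = P(|Z| > 0.5/0.447 = 1.118) = 0.26. On average a fraction r of the gap carries forward: at r = 0.6, a 0.5 SD gap becomes 0.3 SD. This variability is already part of the 0.447, so it is not an additional error. Adjustment removes it.

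**3. Adjustment at one time.** The variance relative to step 1 is (1 − r²) × [1 + 1/(N − 4)]. With N = 20 the second factor is 1 + 1/16 = 1.0625. The half-width is 2.110 × √(0.2 × relative variance), with 17 df.

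| r with that time | relative variance | change | 95% half-width |
|---|---|---|---|
| 0.3 | 0.91 × 1.0625 = 0.967 | −3% | 0.93 SD |
| 0.5 | 0.75 × 1.0625 = 0.797 | −20% | 0.84 SD |
| 0.7 | 0.51 × 1.0625 = 0.542 | −46% | 0.69 SD |
| 0.8 | 0.36 × 1.0625 = 0.383 | −62% | 0.58 SD |

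Break-even is at r² = 1 − 1/1.0625 = 0.059, so r ≈ 0.24. Below that, adjustment costs slightly more than it saves.

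**4. Fading correlation.** If r is the correlation over 24 h and decays geometrically, the correlation between baseline and 72 h is r³.
- r = 0.5: r³ = 0.125, and relative variance = (1 − 0.016) × 1.0625 = 1.05, a 5% loss.
- r = 0.7: r³ = 0.343, and relative variance = (1 − 0.118) × 1.0625 = 0.94, a 6% gain.

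In this case the benefit lies mainly at 24 h.

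**5. Baseline-adjusted average of the three times.** With equal correlations the relative variance is [(1 + 2r)/3 − r²] × 1.0625. This gives 0.47 at r = 0.3, 0.44 at 0.5, 0.33 at 0.7 and 0.24 at 0.8. A simulation of 20,000 trials gave 0.448 and 0.331 at r = 0.5 and 0.7, against 0.443 and 0.329 by formula. With geometric decay the values are 0.50, 0.56, 0.52 and 0.43 for the same r. The reduction is therefore 53–76% or 44–57%, if the effect is the same at all three times and no values are missing.

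If the effect instead grows as 1/3, 2/3 and 1 of its 72 h size, the average captures only 2/3 of it. Each relative variance must then be divided by (2/3)² = 0.444 for a fair comparison with the raw 72 h difference. The results are 1.00 and 0.74 (equal correlation, r = 0.5 and 0.7) and 1.26 and 1.18 (decay, same r), which range from a 26% gain to a 26% loss.

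**6. Schedule.** The Screening marks for laboratory tests and ventilator settings allow a P/F to be assembled. They are separate rows, however, and nothing in the table pairs the FiO2 with the blood gas. The one row that would pair them is blank at Screening.

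**The case against.** The document is silent on baseline adjustment; it does not exclude it. An adjusted analysis also takes the 24, 48 or 72 h level as its outcome, so the endpoint wording is compatible with one, and covariates for a secondary endpoint are often left to an analysis plan. That stands: a reader might infer that the trial has committed to ignoring baseline, and the text does not say so. What remains is that the article does set out its statistical methods, names only unadjusted group summaries, and has a schedule that does not secure the baseline.

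A reader might also infer that half or more of the information in 20 patients is being wasted. The document does not support that. The figure needs a correlation it does not give, an effect that is steady from 24 to 72 h, complete data, and a single-time comparison as reference. For a warming period lasting the full 72 h, an effect that builds up is plausible, and the averaged analysis could then gain nothing or lose.

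Nor does it follow that the three comparisons should be replaced by one average. That changes the question from three time-specific differences to another quantity. It is also undefined for patients who die or are extubated before 72 h. Reporting each time separately is reasonable in a pilot. All three times are named in advance and no tests are planned, so selective emphasis on one of them is not shown.

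Finally, imbalance would be visible in the planned comparison of baseline variables by arm. Seeing an imbalance does not correct the outcome estimate for it.

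**Conclusion.** The point holds in a limited form. The stated P/F analysis makes no use of a pre-treatment value that can be derived from scheduled data. The recording row neither guarantees a value before warming nor reaches the 72 h endpoint. The row leaves a gap in what is scheduled for recording; it does not show that the data will be missing, because blood gases are taken regularly in routine care.

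The size is conditional on r. Adjustment at one time removes roughly 20% of the variance at r = 0.5 and 46% at r = 0.7, and little or nothing at 72 h if correlation fades quickly. Put differently, 20 adjusted patients are worth about 20/0.797 = 25 or 20/0.542 = 37 unadjusted ones at that time point. P/F is a secondary endpoint in a descriptive pilot, so this is a worthwhile improvement and no threat to the trial's validity.

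**What to change.** 1. In the schedule, mark PaO2/FiO2 recording at Screening. Define baseline as the last P/F before randomisation, with FiO2 taken at the time of the blood gas. That anchor exists in both arms.
2. Reconcile the same row with the 72 h endpoint, so that a 72 h value has a place in the table.
3. In *Statistical methods*, add the between-arm difference in P/F with a 95% confidence interval at each of 24, 48 and 72 h, adjusted for baseline. Use ANCOVA at each time, or a repeated-measures model on all available times. Keep the planned descriptive summaries.
4. Report the baseline–follow-up correlation at each time, for sizing the next trial.
5. Optionally, add the baseline-adjusted average over the three times as supportive, and state how deaths and extubations before 72 h are handled.

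The cost is a few lines of text and small edits to one schedule row, with no new procedure. Adjustment uses one degree of freedom and loses a little precision if r is below about 0.25. The article says data collection has not begun, so all of this can still be prespecified.

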### Primary study endpoints

*The primary endpoint of this study will be*:

Viral load measured in lower respiratory tract sample 72 hours after initiation of core warming

*Secondary study endpoints include*:

PaO2/FiO2 ratio 24, 48, and 72 hours after initiation of core warmingDuration of mechanical ventilationDuration of ICU and hospital stayPatient mortality

### Inclusion criteria

Patients above the age of 18 years old.Patients with a diagnosis of COVID-19 on mechanical ventilation.Patient maximum baseline temperature (within previous 12 hours) < 38.3°C.Patients must have a surrogate or legally authorized representative able to understand and critically review the informed consent form.

### Exclusion criteria

Patients with contraindication to core warming using an esophageal core warming device.Patients known to be pregnant.Patients with <40 kg of body mass.Patients with DNR status.Patients with acute stroke, post-cardiac arrest, or multiple sclerosis.

### Subject recruitment

Subjects will be recruited from the ICU or other clinical environment in which they are being treated (Emergency Department, step-down unit, etc.). Patients will be identified by the PI or other study investigators/coordinators as available. All patients without a DNR order with a diagnosis of COVID-19 and meeting inclusion criteria will be eligible for screening for any exclusion criteria. Written informed consent for the research study will be obtained from patient’s surrogate or legally authorized representative prior to enrollment. If a patient enrolled in the study gains the capacity to consent for him/herself while the study is in progress, the patient will be approached by a study team member and the consent document will be presented directly to the patient. All questions the patient might have will be answered. The patient will be given the opportunity to either withdraw from the study or sign the consent form. The patient will be informed that his or her decision to withdraw from the study will not affect his or her medical care

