### Duration of study participation

Participants will be involved for approximately 1 month, including screening, treatment, and follow-up. After consent, patient participation in the intervention phase will last 72 hours for active treatment. The follow up for determination of outcome and duration of mechanical ventilation will occur at 1-month post-treatment. Additional data will be collected via chart review.

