### Total number of subjects and sites

This single-site study aims to recruit and randomize 20 patients. It is expected that up to 30 subjects may be consented in order to produce 20 randomized & evaluable subjects.

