### Sample size and power determination

Based on a prior study in patients with sepsis, a maximum temperature of 38.3°C to 39.4°C was associated with survival (aHR 0.61 [95% CI, 0.39–0.99]) [29]. However, the effect of warming specific to COVID-19 patients remains uncertain, and as such, it is not possible to accurately perform a power calculation for this pilot study. It is believed that a total of 10 patients for each group will yield the sufficient pilot data to make an appropriate conclusion regarding the potential utility of core warming in reducing viral load, improving pulmonary physiology, reducing mechanical ventilation duration, and increasing patient survival. It is anticipated that data from this pilot study can be used for planning future larger studies.

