### Subject population for analysis

All patients enrolled, randomized to a study arm, and completed in the study will be included for analysis.

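### The re-consent step offers only signing or leaving the study, and with a completers-only analysis set any losses through it fall on patients who recovered enough to be asked

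*Protocol article*

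**What the plan says.** Four statements in the protocol article bear on this point.

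- **Entry (Subject recruitment).** "Written informed consent for the research study will be obtained from patient’s surrogate or legally authorized representative prior to enrollment".
- **Re-consent (same section).** The step is triggered "If a patient enrolled in the study gains the capacity to consent for him/herself while the study is in progress". The choice is then: "The patient will be given the opportunity to either withdraw from the study or sign the consent form". No third option is described.
- **Length of participation (Duration of study participation).** A patient's involvement lasts about one month and covers the follow-up period as well as the 72-hour treatment phase. Outcome and ventilation duration are determined one month after treatment. On the source of data the section adds: "Additional data will be collected via chart review".
- **Analysis set (Subject population for analysis).** "All patients enrolled, randomized to a study arm, and completed in the study will be included for analysis".

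The section on total numbers counts in the same terms: "It is expected that up to 30 subjects may be consented in order to produce 20 randomized & evaluable subjects".

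**The concern.** Patients who die or never regain capacity do not reach the re-consent conversation. Those who do reach it have recovered enough to be asked. If the only alternative to signing is to leave the study, and those who leave are not analysed, loss through this step depends on recovery.

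The outcomes exposed are the later ones: ICU and hospital stay, 30-day mortality and, for some patients, ventilation duration. The respiratory samples that the schedule places at days 7 and 14 are also exposed. Most of the clinical outcomes come from the chart, so a patient who wants no more study procedures might well allow them to be recorded. The wording gives no way to say so.

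The pilot's product is a set of estimates for sizing a definitive trial. No hypothesis test is planned, but that does not remove the problem, because a mortality rate inflated by losing survivors would be carried into that calculation. Re-including withdrawn patients at analysis is not enough either, since outcomes never collected cannot be restored.

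**Working it through.** **Inputs from the protocol article**

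- Allocation (Methods): "Patients will be randomized in a 1:1 fashion with 10 patients (Group A) randomized to undergo core warming", with 10 controls. 10 + 10 = 20, which agrees with the stated total.
- Basis of that total (Sample size and power determination): "it is not possible to accurately perform a power calculation for this pilot study". There is no power calculation to reproduce.
- Allowance: up to 30 consented for 20 evaluable, and 1 − 20/30 = 33.3%. This allowance runs from consent, so it does not show how many losses are expected after randomisation.

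**Inputs that are assumed, because the article does not give them:** deaths per arm, and the number of surviving patients who withdraw at re-consent. Those who withdraw are taken to be alive at day 30.

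**Formula for one arm.** With d deaths among 10 randomised and k survivors withdrawn, completers-only mortality is d / (10 − k), against d / 10 with everyone followed.

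| Deaths of 10 | k = 0 | k = 1 | k = 2 | k = 3 |
|---|---|---|---|---|
| 2 | 20.0% | 2/9 = 22.2% | 2/8 = 25.0% | 2/7 = 28.6% |
| 3 | 30.0% | 3/9 = 33.3% | 3/8 = 37.5% | 3/7 = 42.9% |
| 4 | 40.0% | 4/9 = 44.4% | 4/8 = 50.0% | 4/7 = 57.1% |
| 5 | 50.0% | 5/9 = 55.6% | 5/8 = 62.5% | 5/7 = 71.4% |

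Over these cases the shift runs from +2.2 points (2 deaths, 1 lost) to +21.4 points (5 deaths, 3 lost).

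**The same in proportions.** With true mortality m and a share w of survivors withdrawing, observed mortality is m / (m + (1 − m)(1 − w)). For m from 20% to 50% and w from 10% to 30%, the result runs from 21.7% to 58.8%. For m = 40% it is 42.6%, 45.5% and 48.8% at w = 10%, 20% and 30%.

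**Effect on the comparison of arms**

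- Three deaths per arm, two survivors lost from one arm only: 37.5% against 30.0%, a spurious 7.5 points.
- Three deaths per arm, two survivors lost from each: 37.5% against 37.5%. The difference is correctly zero, but both rates are 7.5 points too high.
- Two deaths against four, two survivors lost from each: 25.0% against 50.0%. The difference is 25 points where the true one is 20.

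Equal withdrawal therefore removes much of the distortion from the comparison, but none of it from the absolute rates.

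**If outcomes are kept and everyone is analysed,** the denominator stays at 10 and the shift is zero. Patients who refuse all further collection remain a loss.

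**The case against.** The strongest objection is that the article never says outcome collection ends on withdrawal. A reader might infer from the two-way choice that declining the device or samples also stops follow-up. No section says so, nor that data already gathered are discarded. An article commonly leaves retention of data, and the position of patients discharged before anyone could approach them, to the full protocol and consent form. Neither is shown, so those details are no finding here. What remains is the rule as printed, together with a definition of participation that includes follow-up and an analysis set limited to completers.

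Three further objections stand in part.

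- **Who can leave.** It is tempting to say that only patients who wake up can leave. That is true of the re-consent step, but nothing prevents a surrogate from withdrawing a sedated patient.
- **Asymmetry between arms.** One might argue that warmed patients have an extra reason to leave because a device is in place. It is there for 72 hours, so the argument reaches only those who regain capacity within that window. After it, both arms face the same choice.
- **What is exposed.** The primary endpoint is viral load at 72 hours, and the oxygenation ratios fall at 24, 48 and 72 hours. These are mostly recorded before capacity returns. Ventilation duration will often be known by then too.

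Finally, every magnitude above rests on assumed counts, and the 7.5-point example is smaller than the 10 points that one patient contributes in an arm of 10. That bears on how loudly to press the point. It does not change the direction of the error.

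**Conclusion.** The point holds in a limited form. As worded, the re-consent step has no option between full participation and leaving. Combined with the completers-only analysis set, it makes losses at that step losses of patients who recovered enough to be asked. When those lost are alive at day 30 and the arm has at least one death, observed mortality in that arm can only rise. With an assumed 3 deaths of 10 and 1 to 3 survivors lost, it is 33% to 43% instead of 30%. The effect on the difference between arms is smaller, and largely cancels if withdrawals and mortality are similar.

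The documents do not support the stronger conclusion that the plan will lose recoverers' outcomes, or that it will bias the comparison against warming. Withdrawal frequency and the time at which capacity returns are unknown. The point concerns the later secondary outcomes and the absolute rates handed to the next trial, and it is a worthwhile, inexpensive improvement to the plan.

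**What to change.** **Subject recruitment.** Replace the two-way choice with three: (a) continue fully; (b) decline remaining study procedures but allow chart-based and day-30 outcomes to be collected; (c) decline all further collection. Record the choice, its date and the patient's arm, so that losses can be reported by arm.

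**Subject population for analysis.** Drop the completion condition. Analyse all randomised patients in the arm to which they were assigned, using all the data they permit.

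Both changes are needed: the first keeps the outcomes available, and the second ensures that they are used. The patient may still refuse everything.

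**Cost.** One protocol paragraph and one sentence on the analysis set, matching consent wording with ethics review, and a slightly longer re-consent conversation.
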